### Intake procedure

At intake to the CIU, patients undergo a routine intake interview with a key-worker that includes the Addiction Severity Index [19]. After the completion of the intake interview, patients are informed by the caseworker of the fact that a study of psychopathology is ongoing at the unit. If the patient agrees to receive further information, a researcher is contacted, which immediately comes to the office of the key-worker to meet the patient and schedules an intake interview.

### Baseline interview

At the baseline interview, the interviewer informs the patient of the study, and explains that the study focuses of psychological and behavioural problems that people with substance abuse regularly encounter. He then explains that there are two different interviews, and that patients will be randomly assigned to one of two types. If asked, he will explain that he does not yet know what kind of interview he will conduct the second time they meet, but he will give a further explanation at their second appointment. If the patient gives consent to participate in the study, a brief structured assessment of axis I disorders is conducted. The assessment is kept brief, in order to reduce assessment reactivity, i.e., the effects that assessment can have on treatment outcomes [20].

The instruments used are therefore chosen to be brief, but have strong indications of validity:

• Anxiety/depression is assessed with The Kessler 6 interview [14].

• Attention Deficit/Hyperactivity Disorder is assessed with the Adult ADHD Self-Report Scale [14].

• Illicit substance dependence and alcohol dependence are both assessed by means of the Opiate Treatment Index substance use items [15].

• Severity of alcohol and illicit drug dependence will be assessed by the Severity of Dependence Scale [SDS] [21].

• Personality disorder severity is assessed with the Structured Assessment of Personality – Abbreviated Scale [SAPAS] [22,23].

If the patient does not speak Danish or English well, does not screen positive for substance dependence as indicated by an SDS score of 3 or more for either alcohol or drugs, a feedback session is scheduled, and the patient is informed that based on his data, we wish to give him individual feedback on the next session.

If the patient satisfies inclusion criteria (speaks Danish or English; SDS > 3; gives informed consent), a second interview is scheduled. The interviewer will also schedule a meeting with the researcher conducting follow-up interviews.

The patient is then randomized to either experimental or control conditions.

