### Referral and recruitment

Patients are recruited by caseworkers. The management of the intake unit and the management of the centre have instructed all caseworkers to ask all new referrals or those referred for a change in treatment to participate in the study.

Caseworkers inform patients that the study concerns assessment of psychological problems, behaviour and other disorders, and that patients will be randomly assigned to one of two types of interviews. The primary interviewer later gives detailed information about the study procedure.

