### Second interview – experimental condition

If the patient is randomized to the experimental condition, the second interview will be an assessment of axis II disorders. The patient will first receive a brief description of what personality disorders is, and be given a brief description of personality disorders as inflexible, maladaptive patterns of behaviour that cause significant problems or distress for themselves or others.

The interview will consist of the following elements:

• The Alcohol Use Disorder and Associated Disorders Interview Schedule (AUDADIS) section for avoidant, dependent, obsessive-compulsive, paranoid, schizoid and histrionic personality disorder [24]. Added items taken from the Parker Personality inventory will be taken in to reflect schizotypal personality disorder and narcissistic personality disorder [25].

• The NPI-16 will be added as a measure of narcissism [26].

• The Psychiatric Research Interview for Substance and Mental Disorders (PRISM) [27,28] will be used to assess borderline and antisocial personality disorder.

Following this, patients will be asked if they have any questions, and thereafter the interviewer will proceed with the interview. The interview will contain the following elements.

The interviewer will be trained through role-plays in administering the interview package. For the PRISM, taped interviews will be co-rated to assess the inter-rater reliability of coding.

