### Ethical approval

Institutional Review Boards in Denmark do not approve or disapprove of trials or other studies of psychosocial interventions. The medical director of social medicine in the City of Copenhagen, M.D. [name], read and approved the protocol in Danish. Patients will be given full information about the nature of the study, and be asked to give informed consent. Patients who refuse participation in the study will be given full access to all regular treatment services in the organisation, similar to the control group.

Ethically, the issues related to this study concerns the consequences of receiving serious diagnoses for which there is no clear and simple treatment, in particular personality disorders. However, although there is no simple treatment, patients are given suggestions and support, and have access to the support of the treatment centres

When patients in this trial are assessed, they also receive feedback and advice about how to handle the issues involved, and their caseworkers are given feedback and advice on how to best support patients.

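### The information described before consent does not name personality disorder assessment, and patients who refuse on learning of it could be lost from the experimental arm only

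*Protocol article*

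**What the plan says.** All places are in the Protocol article.

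- **Referral and recruitment:** "Caseworkers inform patients that the study concerns assessment of psychological problems, behaviour and other disorders", and that they will be randomly assigned to one of two interview types. The section adds: "The primary interviewer later gives detailed information about the study procedure".
- **Intake procedure:** the caseworker mentions that research on psychopathology is under way at the unit.
- **Baseline interview:** the interviewer "explains that the study focuses of psychological and behavioural problems that people with substance abuse regularly encounter" and says that there are two interviews, assigned at random. If asked, he answers that he does not yet know which one he will conduct, "but he will give a further explanation at their second appointment". Then: "If the patient gives consent to participate in the study, a brief structured assessment of axis I disorders is conducted". Randomisation comes at the end of this visit.
- **Second interview, experimental condition:** "The patient will first receive a brief description of what personality disorders is".
- **Second interview, control condition:** an open interview on topics the patient chooses. No explanation of personality disorders is described.
- **Withdrawal:** participants who withdraw from trial treatment are not asked back for follow-up, and their records are removed from every file.
- **Ethical approval:** "Patients will be given full information about the nature of the study, and be asked to give informed consent". It also says that "the issues related to this study concerns the consequences of receiving serious diagnoses for which there is no clear and simple treatment", and singles out personality disorders.

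**The concern.** The feature that distinguishes the two arms is an assessment for personality disorders that may end in a diagnosis. The article's own ethics section treats such diagnoses as the sensitive matter in the trial. Yet the wording it describes for use before consent speaks only of psychological and behavioural problems in general.

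Two things are at stake. First, the described information falls short of what Ethical approval promises. Second, a patient who objects to this assessment may learn of it only once allocated to it, while a like-minded control patient may never face the choice. Refusal would then depend on allocation. Taken with the Withdrawal section, that could remove a selected group from the experimental arm and leave its counterpart in the control arm.

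**Working it through.** **Order of events.** The document gives no refusal, attrition or response rate on this point, so there is no stated figure to reproduce. The first check is of sequence.

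| Step | What the patient is described as hearing | Personality disorders named? |
|---|---|---|
| Caseworker, recruitment and intake | Psychological problems, behaviour, other disorders; research on psychopathology; two interviews at random | No |
| Interviewer, before consent | Psychological and behavioural problems; two interviews at random | No |
| Consent, baseline assessment, randomisation | Personality screening items (SAPAS) are given to all; the text does not say patients are told what these measure | Not stated |
| Second interview, experimental | A description of personality disorders | Yes |
| Second interview, control | Topics chosen by the patient | None described |

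So consent and allocation both precede the first explanation the article describes, and it describes that explanation for one arm.

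**What follows for the comparison.** All inputs here are assumed. Let there be no true effect and let the average response be p in both arms. Let a fraction L of patients refuse on learning of the assessment, with response q. They are lost from the experimental arm only.

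- Control arm, complete: p.
- Experimental arm, stayers only: (p − L·q)/(1 − L).
- Spurious difference: (p − L·q)/(1 − L) − p = L·(p − q)/(1 − L).

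With p = 40% and q = 20%:

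- L = 5%: (0.40 − 0.01)/0.95 = 41.1%, a difference of +1.1 points.
- L = 10%: (0.40 − 0.02)/0.90 = 42.2%, a difference of +2.2 points.
- L = 20%: (0.40 − 0.04)/0.80 = 45.0%, a difference of +5.0 points.

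Only the gap p − q enters the last formula, so p = 50% with q = 30% gives the same differences. If q lies 20 points above p, they become −1.1, −2.2 and −5.0. If q = p, the difference is 0.

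**If refusers are kept.** Take L = 10% and q = 20%, and suppose refusers are followed and analysed in the arm to which they were randomised. The experimental arm is then 0.90 × 42.2% + 0.10 × 20% = 38% + 2% = 40%, the same as control. The bias therefore needs two conditions: refusal that depends on allocation, and removal of the refusers from the outcome data. The Withdrawal section supplies the second if declining the second interview counts as withdrawing from trial treatment. That is a natural reading, but the section does not say so.

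**The case against.** The strongest reply is that the article nowhere says personality disorder assessment is kept from patients until after randomisation. Several stronger readings are tempting, and the text does not carry them.

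- **That the content of the interviews is deliberately withheld.** The deferred explanation is offered only if the patient asks, and it mainly concerns which interview will be given. Nobody knows that before allocation, and deferring it is compatible with proper consent.
- **That the passages cannot both be true.** Detailed information from the primary interviewer is promised under Referral and recruitment, with no stated content and no timing beyond a later point. It could be given at consent. A journal article's summary of what is said is also not the consent document, which is not shown.
- **That only experimental patients are ever told.** This is inferred from silence about controls. The further explanation promised for the second appointment is not limited to one arm, and the description that opens the experimental interview is not said to be the first mention.
- **That the arms lose comparability however withdrawals are handled.** The calculation shows otherwise: following refusers and analysing them as randomised removes the bias.
- **That the trial's main risk goes undisclosed in one arm.** The section on risks places the main risk in reacting to feedback about one's own functioning, and both arms receive feedback.

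These points stand and limit the claim. They do not remove it. The article chose to describe what is said before consent, and that description stays general at the very visit where the detail would be expected. The deletion rule under Withdrawal is stated without qualification. The Background also says that patients with personality disorders drop out more and often remain more symptomatic. That makes loss related to prognosis plausible, although refusing the assessment is not the same as having a disorder.

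**Conclusion.** The point holds in a limited form. As written, the described pre-consent information conflicts with the commitment under Ethical approval and with the issue that section itself raises. The conflict may be one of reporting only, and a sentence confirming disclosure at consent would settle that part.

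The statistical consequence is a risk of one-sided loss; the documents do not demonstrate that it occurs. On the assumed figures it shifts the comparison by between 1.1 and 5.0 points in either direction. It vanishes if refusers respond at the average rate or are retained in the analysis. True size and direction are unknown because the document gives no rate of refusal and no response among refusers. This should be considered; it does not reach must-fix.

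**What to change.** 1. Reconcile Referral and recruitment, Baseline interview, Second interview (experimental condition) and Ethical approval. State that, before consent and randomisation, every patient is told that one interview assesses personality disorders and may yield such a diagnosis, and that the other is an open interview about the patient's life situation. Hold back only the hypothesis and which interview is designated experimental. This fits the patient blinding claimed in the Discussion, which covers only that designation. Patients who object then decline before allocation, alike for both arms.
2. Reconcile Withdrawal with analysis as randomised. Separate declining the second interview from withdrawing consent. Patients who decline but do not withdraw consent are still invited to follow-up, kept in the data and analysed in their allocated arm.

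**Cost:** rewording the patient information and one section of the protocol. The consent rate may fall slightly. Control patients, who already hear that there are two interviews, would also know what the other one contains. That could colour their expectations or what they let slip to the blinded follow-up interviewers, so the existing request not to discuss the interview with them becomes more important.

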### Second interview – experimental condition

If the patient is randomized to the experimental condition, the second interview will be an assessment of axis II disorders. The patient will first receive a brief description of what personality disorders is, and be given a brief description of personality disorders as inflexible, maladaptive patterns of behaviour that cause significant problems or distress for themselves or others.

The interview will consist of the following elements:

• The Alcohol Use Disorder and Associated Disorders Interview Schedule (AUDADIS) section for avoidant, dependent, obsessive-compulsive, paranoid, schizoid and histrionic personality disorder [24]. Added items taken from the Parker Personality inventory will be taken in to reflect schizotypal personality disorder and narcissistic personality disorder [25].

• The NPI-16 will be added as a measure of narcissism [26].

• The Psychiatric Research Interview for Substance and Mental Disorders (PRISM) [27,28] will be used to assess borderline and antisocial personality disorder.

Following this, patients will be asked if they have any questions, and thereafter the interviewer will proceed with the interview. The interview will contain the following elements.

The interviewer will be trained through role-plays in administering the interview package. For the PRISM, taped interviews will be co-rated to assess the inter-rater reliability of coding.

### Second interview: control condition

The control condition will contain an interview of up to one hour, where the patient chooses focus based on a list of items (substance use problems; family; friends; work/education; etc). The interview is client-driven and follows an ethnographic approach.

These interviews are taped and used as the basis for a condensed summary in the feedback

### Randomization and blinding

Randomization will be conducted by means of a predefined list of random numbers, stratified by predefined characteristics, which will not be disclosed at this point to reduce risk of breaking of blind. Randomization is executed according to a list, the allocation sequence of which was computer-generated by one of the researchers (MH). The interviewer will be blinded to randomization at the baseline interview.

The follow-up interviewers will be introduced to the patients at the baseline interview, to assure blinded follow-up assessments.

### Withdrawal

A participant can withdraw from the trial at any point, although information already given to caseworkers cannot be withdrawn. Participants who withdraw from the trial treatment will not be asked to attend the follow-up appointments, and will be deleted from all files.

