### Inclusion criteria

To be eligible for the study, patients must satisfy the following criteria:

• Be at least 18 years of age.

• Not currently be psychotic or have a known diagnosis of schizophrenia excluding patients from treatment at the intake unit.

• Not currently be involved in an ongoing treatment for a drug or alcohol problem. Patients who are currently involved in treatment for alcohol or drug abuse will, however, not be referred to the CIU.

• Have past-year substance dependence, as indicated by a score on the SDS of 3 or more for either alcohol or drugs.

• Speak Danish or English fluently.

• Give informed consent.

The assessment and feedback takes place in the first three weeks of treatment.

Table 1 gives an overview of the interviews and questionnaires conducted at the different assessment times. Figure 1 represents the research procedure schematically. Figure 2 contains the expected participant flow.

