### Outcome criteria

The main outcome criterion will be the following: Improvement in at least one of the following areas, described as a 30% decline in score, with no concurrent deterioration in any area: global functioning, as measured by the Work and Social Adjustment Scale [12]; psychiatric symptoms, as measured by the Kessler 6+ [13,14]; substance use, as measured by the Opiate Treatment Index drug use indicator [15]; treatment engagement, as measured by treatment staff, using the treatment engagement scale from DATOS [16].

Secondary outcome criteria will be

• Retention in treatment, defined as being retained in the same treatment that patients were first referred to after their contact with the intake unit at 3 and 6 months follow-up, or having completed that treatment as planned.

• Understanding of one's own personality and the impact that personality has on others, as rated by an independent interviewer [17].

• Readiness to change dysfunctional behaviour, work with emotional problems, change illicit drug use, and change alcohol use, as measured by brief 4-item questions, adapted from the smoking cessation literature [18].

Outcome criteria will be assessed at 3 and 6 months follow-up.

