### Risks and anticipated benefits for trial participants and society, including how the benefits justify the risks

Patients with substance use disorders and co-morbid personality disorder experience a number of serious problems. Patients with co-morbid personality disorder tend to remain symptomatic long after treatment [7,8], and patients with some co-morbid personality disorders tend to commit a substantial amount of the crime that substance abusers commit [31].

If the findings of this study show that personality assessment can significantly improve the functioning of patients with substance use disorders, this can have significant impacts on both the quality of life of patients, and on society.

The main risk of this study is that patients experience a worsening of psychiatric symptoms or substance use as a reaction to receiving a feedback concerning their own personal functioning. There is some indication that symptoms may fail to improve with focus on personality, even if this focus improves substance use and therapeutic alliance [9]. We will monitor psychiatric symptoms every 3 months during the study, and patients have access to caseworker, psychiatrist and psychologist at the treatment centre.

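### The withdrawal rule merges leaving the trial treatment with withdrawing consent to data use, so randomised patients are neither followed up nor kept in the data

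*Protocol article*

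**What the plan says.** The Withdrawal section has two sentences. The first allows withdrawal at any time: "A participant can withdraw from the trial at any point, although information already given to caseworkers cannot be withdrawn". The second sets the consequence: "Participants who withdraw from the trial treatment will not be asked to attend the follow-up appointments, and will be deleted from all files". The trigger in the second sentence is leaving the trial treatment, a term the article does not define. Deletion is not made conditional on a request from the patient, and nothing elsewhere in the article softens the rule.

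The section on risks and anticipated benefits names as the main risk that "patients experience a worsening of psychiatric symptoms or substance use as a reaction to receiving a feedback" about their own functioning. It then promises: "We will monitor psychiatric symptoms every 3 months during the study".

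**The concern.** Withdrawal here can happen after randomisation. Deleting everyone who withdraws means that the groups compared at 3 and 6 months are no longer the groups that were randomised.

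There is a plausible route by which withdrawal could depend on arm. Both arms receive feedback (Design), but only the experimental arm has the Axis II interview from which personality disorder diagnoses are fed back (Second interview – experimental condition). The Ethical approval section itself raises the consequences of giving such diagnoses. If patients who react badly leave, and leave more often in one arm, the remaining patients give a distorted comparison.

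Deletion is also irreversible. The planned mixed effects ordinal regression with baseline covariates (Outcome evaluation) can use only records that exist. Once baseline values are gone, withdrawers cannot be imputed, compared with completers or entered in a sensitivity analysis. Their data for the retention outcome are lost as well. This is a fixed rule on data collection and retention, not a detail that an analysis plan could settle later.

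**Working it through.** The article states no withdrawal rate, expected response or sample size, so there is no figure to reproduce. The check has two parts.

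**Order of events**

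1. The baseline interview ends with allocation: "The patient is then randomized to either experimental or control conditions" (Baseline interview).
2. Exposure follows: "The assessment and feedback takes place in the first three weeks of treatment" (Inclusion criteria).
3. Measurement comes later: "Outcome criteria will be assessed at 3 and 6 months follow-up" (Outcome criteria).
4. Withdrawal is allowed at every stage (Withdrawal).

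The rule therefore reaches patients who leave between randomisation and the second interview. If withdrawal after feedback also counts, it reaches patients already exposed, and anyone who leaves between the two follow-ups would lose the 3-month data too.

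**Illustration of size (all inputs assumed)**

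Let *r* be the true response rate in an arm, *w* the share withdrawn and deleted, and *q* the response rate among withdrawers. The rate observed after deletion is

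(r − w × q) / (1 − w)

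With r = 0.50 in both arms and q = 0, this is 0.50 / (1 − w). Differences are taken from unrounded rates.

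| Withdrawn, experimental v control | Observed, experimental | Observed, control | Difference (points) |
|---|---|---|---|
| 5% v 5% | 0.50/0.95 = 52.6% | 0.50/0.95 = 52.6% | 0 |
| 10% v 5% | 0.50/0.90 = 55.6% | 52.6% | +2.9 |
| 15% v 5% | 0.50/0.85 = 58.8% | 52.6% | +6.2 |
| 20% v 5% | 0.50/0.80 = 62.5% | 52.6% | +9.9 |
| 5% v 15% | 52.6% | 58.8% | −6.2 |

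If withdrawers respond like everyone else (q = 0.50), the observed rate is (0.50 − 0.50w)/(1 − w) = 0.50 for any w, and the difference is 0.

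The same formula applies to deterioration, where a negative difference flatters the experimental arm:

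- **No true effect, 20% deterioration in both arms, half of withdrawers deteriorating, withdrawal 15% v 5%:** (0.20 − 0.15 × 0.50)/0.85 = 14.7% against (0.20 − 0.05 × 0.50)/0.95 = 18.4%, a difference of −3.7 points. It is −1.8 at 10% v 5% and −5.9 at 20% v 5%.
- **True harm of 25% v 20%, withdrawal 15% v 5%:** with half of withdrawers deteriorating, 20.6% v 18.4%, so +2.2 instead of +5. With 80% deteriorating, (0.25 − 0.12)/0.85 = 15.3% v (0.20 − 0.04)/0.95 = 16.8%, so −1.5 and the sign is reversed. With 20% deteriorating, (0.25 − 0.03)/0.85 = 25.9% v 20.0%, so +5.9 and the harm is slightly overstated.

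If all randomised patients are kept and followed up, w = 0 and the expected observed difference equals the true one in every scenario.

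**The case against.** **The trigger is ambiguous.** The intervention is short and over within the first weeks, so after feedback there is little trial treatment left to abandon. The first sentence of the section speaks of leaving the trial, and its remark about information already passed to caseworkers suits a participant taking back consent and data. On that view the rule is a loosely worded consent provision. This is a fair reading, and the article does not say that a missed second interview or feedback session counts as withdrawal. But the sentence that orders deletion does not say it is about consent. Two kinds of withdrawal are merged, which is the fault.

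**Some stronger inferences are not supported.**

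- *That the rule hides the main harm altogether.* It does not. K6, WSAS and OTI are measured at follow-up in patients who stay, and the outcome score runs down to −3 for deterioration in all areas. Only worsening among withdrawers is lost. The risks section also gives patients access to clinical staff.
- *That withdrawals by arm can never be counted.* Allocation follows a predefined list (Randomization and blinding). If that list survives, used allocations minus remaining records may give the counts. The article does not ensure this, but does not rule it out.
- *That the rule flatly contradicts the monitoring promise.* That promise is limited to the duration of the study, and a patient who has left may be regarded as outside it. The two sections are in tension and need reconciling.
- *That the bias favours the experimental arm.* Control patients also receive feedback, on Axis I disorders, and no withdrawal rates are given. The direction is open.

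**The illustration is simple.** It treats outcome as binary, whereas the Outcome evaluation section plans an ordinal score. That limits it to showing how large the distortion could be.

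**Conclusion.** The concern stands in this form: the Withdrawal section ties loss of follow-up and deletion of data to leaving the trial treatment, without separating this from withdrawal of consent to data use. As written, it removes randomised patients, rules out a full intention-to-treat analysis and any sensitivity analysis of withdrawers, and loses any worsening among them. That sits badly with the named main risk and with the 3-monthly symptom monitoring.

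Whether the treatment comparison is biased depends on two conditions: withdrawal must be related to outcome, and it must differ between arms in how many withdraw or in who withdraws. Both are plausible here; neither is established. Under the assumed inputs the distortion in response runs from 0 to +9.9 points, and to −6.2 in the one reversed case worked. These figures are not estimates for this trial. The rule should be changed because it is irreversible and cheap to correct.

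**What to change.** Rewrite the Withdrawal section to separate three events:

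- **(a) Stopping the second interview or feedback.** Still invite the patient to both follow-ups, keep all data and analyse as randomised.
- **(b) Declining further follow-up.** Keep the data already collected and analyse as randomised.
- **(c) Withdrawing consent to data use.** Delete only on the patient's explicit request, and keep an anonymous count by arm.

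Report withdrawals by arm, and reconcile the section with the monitoring statement in the risks section so that it is clear which patients are monitored.

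The cost is one amended paragraph, matching consent wording and some extra follow-up invitations; follow-up interviewers are already part of the design. The new consent text can apply only to patients enrolled from then on. Deletion already promised to earlier participants must be honoured unless they re-consent.
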